## Abstract

**Background:**

Breastfeeding provides ideal infant nutrition, conferring several health benefits to children and their mothers. Women with inverted nipples, however, face difficulties that force them to prematurely terminate breastfeeding. Whereas available conservative measures for the correction of inverted nipples are of limited success, the use of an inverted syringe may be effective in achieving high rates of infant latching and exclusive breastfeeding. This technique, however, has not been investigated in a clinical trial.

**Methods/design:**

This open-label randomized controlled trial aims to investigate whether, in women with inverted nipples, the use of an inverted syringe increases the rate of exclusive breastfeeding at one month compared to standard care. One-hundred healthy women with grade 1 or 2 inverted nipples will be recruited as of 37 weeks of gestation. They will be randomly allocated to standard care (control group) or to an intervention group. The intervention consists of using an inverted syringe to evert the nipple before every breastfeed, starting with the first feed after delivery. The primary outcome measure is the rate of exclusive breastfeeding at 1 month. Secondary outcome measures include exclusive breastfeeding rates at 3 and 6 months, nipple eversion rate, successful latching rate, rates of any breastfeeding at 1, 3, and 6 months, breastfeeding-associated complications, maternal satisfaction with breastfeeding, maternal quality of life, and adverse events. Descriptive and regression analysis will be conducted under the intention to treat basis.

**Discussion:**

The use of the inverted syringe to evert inverted nipples is a simple, inexpensive, and safe technique that can be performed by mothers with inverted nipples. Findings of this trial, if positive, will provide much needed evidence for a safe, affordable, readily available, and simple intervention to treat inverted nipples, and improve breastfeeding practice among affected women.

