#### Secondary outcome measures

Secondary outcomes include differences between the two groups in the rates of nipple eversion at 1 month, successful latching of the infant on mother’s breast at 1 month, exclusive breastfeeding at 3 and 6 months, mixed feeding at 1, 3, and 6 months, breastfeeding-associated complications such as sore nipple, mastitis, pain, bleeding, and breast engorgement at 1 week, 1, 3, and 6 months postpartum. Other secondary outcomes are maternal satisfaction with breastfeeding assessed at 1 week postpartum using the validated Maternal Breastfeeding Evaluation Scale [18, 19], and maternal quality of life assessed at 1 month using the validated Postpartum Quality of Life instrument [20] (Fig. 1).

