### Sample size

Based on data from a previous breastfeeding clinical trial that we conducted, 45% of women continue to breastfeed exclusively for 1 month postpartum [21]. We hypothesize that in women with inverted nipples, 40% of the experimental group and 5% of the control group will be exclusively breastfeeding at 1 month. To have 90% power and 5% type I error, and using the online calculator available at http://powerandsamplesize.com/Calculators/Compare-2-Proportions/2-Sample-Equality, we will need 25 women in each group to detect this 35% difference in the exclusive breastfeeding rates between the two groups.

In our recent breastfeeding support trial [21], the attrition rate was 40%. Since women with inverted nipples face more difficulties in breastfeeding than women with normally everted nipples, we hypothesize that 50% attrition rate would be a reasonable assumption for the proposed study. To account for a potential attrition rate of 50%, we inflated the sample size to become 100 women in total.

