### Statistical methods

We will compare continuous variables using Student’s *t* test and categorical variables using Chi square test. Non-parametric tests will be used to analyze variables with skewed distribution or when the number of analyzed subjects is less than 30. We will calculate the crude rates of exclusive breastfeeding and mixed feeding at 1, 3, and 6 months in both groups. The 95% confidence intervals for the crude rates of breastfeeding will be computed using the normal approximation to the binomial distribution. We will also conduct multivariable logistic regression analysis to investigate the association between exclusive breastfeeding at 1 month (dependent variable) and the use of the inverted syringe (predictor) adjusting for potential confounders such as the grade of inverted nipple. Missing data will be imputed using last observation carried forward for the breastfeeding outcomes at 1, 3, and 6 months if breastfeeding was discontinued on last follow-up, the average value for continuous variables, and random replacement to maintain proportions for categorical variables, as appropriate. We will conduct sensitivity analysis with and without the imputed missing data to assess the impact of missing data on the primary outcome. We will also conduct repeated measurement analyses using generalized estimating equations (GEE) to explore the effect of the intervention over time. Blinded, intention to treat analysis will be conducted using the Statistical Package for Social Sciences (SPSS) version 24. A *p* value of < 0.05 will indicate statistical significance.

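### The article says a positive trial will give evidence that the syringe is safe, but it attaches no harm condition to that word, and a trial sized only for exclusive breastfeeding cannot exclude a sizeable excess of complications

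*Protocol article*

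**What the plan says.** The Discussion part of the Abstract makes two statements about safety. The first is made before any data: the technique "is a simple, inexpensive, and safe technique that can be performed by mothers with inverted nipples". The second concerns what the trial will show: "Findings of this trial, if positive, will provide much needed evidence for a safe, affordable, readily available, and simple intervention to treat inverted nipples".

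What counts as positive is not defined. The aim and the sample size concern one efficacy endpoint: "The primary outcome measure is the rate of exclusive breastfeeding at 1 month". Under Sample size the authors conclude that "we will need 25 women in each group to detect this 35% difference in the exclusive breastfeeding rates between the two groups", and they then inflate to 100 women in total for 50% attrition.

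Harms are planned for. The Abstract's secondary outcomes include "breastfeeding-associated complications, maternal satisfaction with breastfeeding, maternal quality of life, and adverse events". Secondary outcome measures lists between-group differences in "breastfeeding-associated complications such as sore nipple, mastitis, pain, bleeding, and breast engorgement at 1 week, 1, 3, and 6 months postpartum". Data collection includes adverse events at months 3 and 6, and Ethics approval says adverse events go to the IRB.

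Statistical methods gives one general criterion, a p "value of < 0.05 will indicate statistical significance", with chi-square for categorical variables. On intervals it says only this: "The 95% confidence intervals for the crude rates of breastfeeding will be computed using the normal approximation to the binomial distribution". No harm hypothesis, acceptable excess or interval for a harm difference is stated.

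**The concern.** Success on exclusive breastfeeding says nothing about safety. Safety needs its own evidence, namely an upper limit on how much extra harm is compatible with the data. The article promises that evidence as a product of a positive trial without saying what harm result would support or contradict it.

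The question is open for this technique. The Abstract says it has not been investigated in a clinical trial. The only experience the Background describes is a case series of eight women. Nipple pain, soreness and bleeding are outcomes of the trial itself.

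At stake is the wording of the results paper and of the advice built on it. If harms are summarised only by p-values, a non-significant comparison could sit beside the word safe although the data remain compatible with a large excess.

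**Working it through.** **Inputs from the article.** Sample size: 40% v 5%, 90% power, 5% type I error, 25 evaluable women per group, 50% attrition, 100 in total. Randomization: 1:1, so 50 per arm if nobody is lost. Statistical methods: chi-square and p < 0.05. Sidedness is not stated, so two-sided is assumed.

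**Inputs assumed.** The article gives no complication rate. Control rates of 10%, 20% and 30% are assumed, each doubled in the syringe arm.

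**Step 1: reproduce the planned size.** Unpooled normal formula:

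n = [p1(1−p1) + p2(1−p2)] × [(1.960 + 1.282)/(p1−p2)]²
= [0.40×0.60 + 0.05×0.95] × [3.242/0.35]² = 0.2875 × 85.8 = 24.7, rounded up to 25 per group.

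50/(1−0.5) = 100 in total. Both figures reproduce. Exact enumeration of the uncorrected chi-square test at 5% v 40% with 25 per arm gives power 0.907, in line with the planned 90%. The same method is used in Step 2.

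**Step 2: chance of missing a doubling.** Sum the probabilities of all pairs of binomial counts for which the chi-square test is significant, and subtract from 1.

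| Control → syringe | Power, 25/arm | Missed | Power, 50/arm | Missed |
|---|---|---|---|---|
| 10% → 20% | 0.174 | 83% | 0.303 | 70% |
| 20% → 40% | 0.352 | 65% | 0.595 | 40% |
| 30% → 60% | 0.622 | 38% | 0.876 | 12% |

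By the normal approximation, power for a doubling passes 50% at a control rate of about 27% with 25 per arm and about 17% with 50. Fisher's exact test would have less power: for 20% → 40% with 25 per arm, 0.231 instead of 0.352.

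**Step 3: what an apparently reassuring result would exclude.** This step needs no doubling scenario. Suppose both arms show 20%.

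- 25 per arm (5/25 in each): the Wilson 95% limits for one arm are 8.9% and 39.1%. The Newcombe limit for the difference is ±√[(0.200−0.089)² + (0.391−0.200)²] = ±0.22.
- 50 per arm (10/50 in each): the Wilson limits are 11.2% and 33.0%. The Newcombe limit is ±√[(0.200−0.112)² + (0.330−0.200)²] = ±0.16.

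**Step 4: zero events in the syringe arm.** The one-sided 95% upper bound is 1 − 0.05^(1/n). For n = 25 it is 11.3%. For n = 50 it is 5.8%.

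**The case against.** The strongest reply is that safety is a premise here and not a planned inference. In the quoted sentence it stands in a list with affordability, availability and simplicity, none of which the trial tests, and the sentence before it already calls the technique safe. The main-text Discussion frames the aim as breastfeeding success and asks for replication even after positive findings. The article is condensed, harms are collected and compared at four time points, and the interval method for harms could sit in a fuller analysis plan.

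Much of this is fair, and it rules out three stronger readings.

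- A reader might infer that the trial will declare the syringe safe because a harm comparison is non-significant. Nothing in the article says so: the threshold is general, and what counts as positive is undefined.
- A reader might infer that harms play no part. They are secondary outcomes. What is missing is a harm condition attached to the word safe.
- A reader might infer that a doubling of complications would usually be missed, or that the result would look much the same whether or not the syringe did harm. That holds only towards low control rates. With no true difference the test is non-significant about 95% of the time. With 20% → 40% at 25 per arm it is non-significant 65% of the time, and with 30% → 60% at 50 per arm only 12%. Ethics approval describes controls as at raised risk of these complications, so low control rates cannot be taken for granted.

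The premise reading does not rescue the sentence. The article says the technique is untested in a trial, cites eight women, and makes harms an outcome of this trial. It cannot assume the property and also present the trial as evidence for it. Nor is the point about missing detail: the article states the conclusion itself.

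**Conclusion.** The point holds in a limited form. The Abstract's conclusion goes further than the stated design and analysis can support: it claims evidence of safety from a trial sized for a 35-point efficacy difference, with no harm condition and no interval named for any harm difference.

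The size of the problem depends on how common the complication is. Detection of a doubling is poor at an assumed control rate of 10%, with a miss rate of 70% to 83%. It is intermediate at 20% (40% to 65%) and better at 30% (12% to 38%). Each range runs from all 50 women per arm evaluable to the planned 25. Independently of those scenarios, equal observed rates of 20% could not exclude an excess of about 16 to 22 points, and zero events could not exclude a rate of 5.8% to 11.3%.

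These figures rest on assumed complication rates and a two-sided uncorrected chi-square test. The primary analysis and its sample size are not affected.

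**What to change.** 1. In the Abstract's Discussion, limit the sentence on positive findings to effectiveness, and do not state safety as established.
2. In Statistical methods, add that each complication and adverse event will be reported as a between-group risk difference with a 95% interval suited to small counts (Newcombe, for example), and that an exact upper bound will be given where the syringe arm has no events.
3. Add that any safety statement will rest on the excess harm that the upper limit excludes, and not on a non-significant test.

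The cost is a few sentences and one more column in the harms table, with no extra patients or data. The downside is that the intervals will be wide and the article can no longer promise evidence of safety.

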**Trial registration:**

ClinicalTrials.gov, NCT03529630. Registered May 8, 2018.

## Background

Breastfeeding confers several health benefits to infants and their mothers, including protection from infectious and chronic diseases, improved child cognition, development, and intelligence, and decreased risks of maternal depression and malignancies [1–5]. As such, breastfeeding is recommended as the exclusive nutrition for the first 6 months of the infant’s life, with continuation until 2 years complemented with solid foods [6–8]. However, women with inverted nipples often have difficulties in maintaining breastfeeding due to improper infant latching that my cause insufficient milk extraction and poor infant satiety, thus leading to early termination of breastfeeding. Congenital inversion of the nipple, the most common nipple deformity, is due to early developmental arrest [9], with an estimated prevalence of about 10% [10]. However, nipple inversion can also be acquired secondary to mastitis, macromastia, carcinoma, or breast reduction, or can be associated with congenital syndromes such as Robinow and MR/MCA syndromes [11]. Han and Hong categorized the severity of inverted nipple into three grades. In grade 1, the nipple is easily pulled out manually, maintains good projection, and has minimal fibrosis. Grade 2 includes the majority of inverted nipple cases in which the affected nipple can be pulled out manually but fails to maintain projection and has moderate fibrosis beneath it. Grade 3 constitutes the rarest type of inverted nipples, which cannot be pulled out manually due to severe fibrosis [12].

The main treatment of inverted nipples is corrective surgery with sectioning of the lactiferous ducts. However, surgery is reserved for the severe grades such as invaginated nipples that are difficult to extract manually (grade 3), and it is not indicated for mild umbilicated nipples that can be momentarily extracted from their inverted positions (grades 1 and 2) [12]. Several non-surgical interventions have been used to extract inverted nipples. Hoffman exercises and the use of Woolwich breast shields, which were routinely recommended, have been shown to be of limited success [13]. The Niplette™ (Philips Avent, Andover, MA, USA) is another simple device that uses gentle negative suction to stretch the lactiferous ducts and extract the nipple with a success rate close to 80% [14]. It consists of a nipple cover, valve, and syringe and is operator dependent with one Niplette needed for each breast [14]. A more recent intervention was described by Chakrabarti and Basu in which a rubber band was put around the nipple base using a syringe applicator with a success rate of 62% [15]. However, this method carries with it certain risks, such as nipple injury, infection, or slipping of the band into the infant’s mouth [15]. The simplest, least expensive, most readily available, and most effective method to extract nipples has been reported in a case series by Kesaree et al. [16]. In this method, women with inverted nipples are trained to use an inverted syringe and apply gentle negative pressure around the nipple to evert it. The procedure can be repeated before each breastfeed as long as required. Of the eight women reported by Kesaree et al., seven (87.5%) infants succeeded in latching within 2 to 7 days, and six (75%) were exclusively breastfeeding at 6 weeks [16]. The main advantage of the inverted syringe over the Nipplette™ and the rubber and syringe technique is the fact that syringes are readily available in all countries, inexpensive, safe, and simple to use. To our knowledge, breastfeeding success with the use of the inverted syringe has not been previously investigated in a clinical trial. In this study, we aim to conduct the first randomized controlled trial to investigate whether the use of the inverted syringe in healthy term pregnant women with inverted nipples improves breastfeeding initiation and continuation rates, as compared to standard care.

## Methods/design

### Study design

The study protocol is designed in accordance with the Standard Protocol Items: Recommendations for Interventional Trials (SPIRIT; Additional file 1) [17]. This is a single-center, open-label, parallel-arm, randomized clinical trial that aims at investigating whether nipple suction exercises using the inverted syringe technique will improve exclusive breastfeeding rates at 1 month postpartum in women with inverted nipples.

### Study population

Eligible subjects are healthy pregnant women, at or above 18 years of age, with grades 1 or 2 inverted nipples. Inclusion criteria are gestation at 37 weeks or more, intention to breastfeed, and residing in Lebanon for 6 months after delivery. We will exclude women with grade 3 inverted nipples, previous breast surgery affecting the breast anatomy, high risk pregnancies, medical conditions that may interfere with breastfeeding, including a critical maternal condition, newborns with congenital malformations such as esophageal atresia, cleft lip, and/or palate, and women choosing artificial milk as their preferred infant nutrition. Women with term twin gestation will not be excluded.

### Recruiting process

Eligible pregnant women will be recruited from the Women’s Health Center and the Delivery Suite of the American University of Beirut Medical Center, Beirut, Lebanon. An inverted nipple is defined as a condition in which the nipple is pulled inward into the breast instead of pointing outward, classified according to Han and Hong [12]. During regular working hours, a trained research assistant will recruit eligible women after explaining the trial’s objective and procedures and verifying inclusion criteria. Written informed consent will be obtained from all participants.

### Randomization

We will randomly allocate eligible women to one of two parallel groups (experimental and control) in a 1:1 ratio according to a computer-generated random sequence. An independent statistician will prepare a set of sequentially numbered opaque sealed envelopes of the allocation group according to the generated random sequence to preserve randomization concealment. A participant’s group allocation will be revealed after verifying that the inclusion/exclusion criteria are met, and after written consent is obtained on the first day postpartum. This will avoid any selection bias introduced by the investigator knowing the allocation of the next subject.

### Description of the interventions

#### Control group

Women in the control group will receive standard medical care during pregnancy and postpartum as dictated by their obstetricians. Any advice regarding infant nutrition or treatment of inverted nipples will be left to the primary physician, including possible use of the syringe technique, in which case the participant will continue in the study and will be analyzed in her group as dictated by the intention to treat principle. We will provide the participants in the control group with documentation on breastfeeding-associated complications, use of artificial devices to correct the inverted nipple, such as nipple shields, Niplette, inverted syringe, or breast pump, and the number of artificial milk feeds given to the newborn with their justification in a diary. The research assistant will send weekly reminders to the participants in the control group using e-mail, telephone messages, or communication through social media, to remind them about documentation in the diary.

#### Intervention group

We will train the participants allocated to the experimental group on the use of the inverted syringe before each breastfeed as of the first postpartum day. We will also provide them with documentation on the daily use of the syringe, adverse events, breastfeeding-associated complications, use of artificial devices to correct the inverted nipple, the number of artificial milk feeds given to the newborn with their justification in a diary. The research assistant will send weekly reminders to the participants in the experimental group to use the syringe technique before each breastfeed using e-mail, telephone messages, or communication through social media. Syringe use will continue for as long as needed by the mother.

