### Data collection

At baseline, we will collect information on socio-demographics such as maternal age, parity, education, employment, family monthly income, previous breastfeeding, and longest duration of previous breastfeeding if present. Data on gestational age, mode of delivery, newborn’s gender, birth weight, APGAR score, and nursery admission status (regular vs intensive care), as well as grading of maternal nipple inversion will be recorded.

On the first day postpartum, the following information will be collected: exclusive breastfeeding (yes/no), use of artificial milk (number of feeds in 24 h, justification), sore nipple (yes/no), pain while breastfeeding (yes/no), compliance with the use of the syringe technique before each breastfeed (experimental group only), and the use of other conservative methods to pull out the nipple (in both groups).

On the third and seventh days postpartum, we will call the participants to remind them about documentation in the diary, collect data about maternal breastfeeding evaluation (day 7 only), and address any questions.

The diary will be collected at 30 and 40 days during the participant’s postpartum visit to her obstetrician. We will also administer the Postpartum Quality of Life instrument, and collect data on the infant’s weight at month 1 from the infant’s health record. The eversion of the nipple will also be assessed by the research assistant during this visit.

On months 3 and 6 postpartum, we will call the participants to collect information on infant feeding methods, adverse events, and infants’ weight at 3 and 6 months.

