### Ethics approval

This study is approved by the Institutional Review Board (IRB) of the American University of Beirut. Written informed consent will be obtained from all participants. Since the study involves using the inverted syringe technique and documentation of relevant data in a diary, we estimate that the risks to women from participating in this study are negligible, not exceeding those of current standard practice. The only risk from nipple manipulation in the experimental group is the rare possibility of uterine contractions and labor induction if done prior to delivery. Since participants will start using the syringe right after delivery, this risk is eliminated. We also anticipate that the use of the syringe will result in less pain and less sore or bleeding nipples in the experimental group compared to the control group, who are at much greater risk for these complications secondary to poor infant latch. We will collect information on any adverse events during follow-up of participants, and will report all adverse events to the IRB as per institutional policies. Should any adverse events result directly from this study, the investigators’ institution will cover the cost of treating, on its premises, those medical adverse events.

Confidentiality of participants will be secured by storing the hard copies of the data collection forms in locked cabinets in the principal investigator’s office (MN). Access to electronic data stored in the SPSS data file will be password-protected, and restricted to the principal investigator (MN). The blinded analyst will be provided with a de-identified dataset to preserve confidentiality. Data will be stored for 5 years after publication of the study findings.

We will report any important modifications of the protocol to the IRB, trial participants, and trial registry. The trial’s results will be disseminated to healthcare professionals and the public through publication in a refereed journal, trial registry, and medical conferences.

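### The experimental-arm diary prompts for adverse events and the control-arm diary does not, so first-month adverse events are ascertained unequally

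*Protocol article*

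**What the plan says.** The Intervention group section says that experimental participants keep a diary with "documentation on the daily use of the syringe, adverse events, breastfeeding-associated complications, use of artificial devices" and artificial milk feeds. The Control group section gives the corresponding list as "documentation on breastfeeding-associated complications, use of artificial devices to correct the inverted nipple", again with artificial milk feeds. Adverse events do not appear in it.

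On timing, the Data collection section states that "The diary will be collected at 30 and 40 days during the participant’s postpartum visit to her obstetrician". On days 3 and 7, "we will call the participants to remind them about documentation in the diary"; the day-7 call also collects the breastfeeding evaluation. At months 3 and 6 the callers "collect information on infant feeding methods, adverse events" and infant weight, with no restriction by arm.

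On outcome status, the Abstract's list of secondary outcomes ends with "maternal satisfaction with breastfeeding, maternal quality of life, and adverse events". The Secondary outcome measures section has no adverse-event outcome. It has "breastfeeding-associated complications such as sore nipple, mastitis, pain, bleeding, and breast engorgement at 1 week, 1, 3, and 6 months postpartum". The Ethics approval section adds a general commitment: "We will collect information on any adverse events during follow-up of participants".

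**The concern.** A between-arm comparison of adverse events is fair only if both arms are asked the same question, in the same way, at the same times. Here the article gives both diary lists in full, and they differ on an item that the Abstract treats as an outcome. Daily syringe use has an obvious reason to be arm-specific. Adverse events have none.

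The article describes the technique as safe and its risks as negligible and no greater than those of standard practice. Unequal prompting would produce an apparent excess on the syringe even with identical true risks, or would leave a difference that nobody could interpret. The trial is open-label, and its Discussion section concedes a possible increase in detection bias, so identical prompts matter more than usual. Control women may also use the syringe on their physician's advice. Their diary records that use but, as listed, has no place for an adverse event arising from it.

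**Working it through.** **1. Compare the stated sources of adverse-event data by arm.** All entries come from the Description of the interventions and Data collection sections.

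| Source | Experimental | Control |
|---|---|---|
| Diary (collected at 30 and 40 days) | syringe use, adverse events, complications, devices, milk feeds | complications, devices, milk feeds |
| Day 1 | feeding, sore nipple, pain, other methods, syringe compliance | same, without syringe compliance |
| Day 3 and 7 calls | no adverse-event question stated | no adverse-event question stated |
| 1-month visit | no adverse-event question stated beyond the diary | no adverse-event question stated |
| Month 3 and 6 calls | adverse events asked | adverse events asked |

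The diary is therefore the only stated first-month prompt for adverse events, and it exists in one arm. Diary reminders do not close the gap, because they refer each woman to a diary whose listed items differ by arm.

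**2. Identify which events are affected.** Complications are in both diaries, and the outcome section illustrates them with sore nipple, mastitis, pain, bleeding and engorgement. Those events have a record in each arm. Two groups remain:

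- events that are not breastfeeding-associated complications;
- events that could be entered under either heading.

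The second group is not empty. The outcome section's list of complications gives examples and is not closed. Complications are also due at 3 and 6 months, yet the calls at those times name adverse events and no separate complications item. The article does not keep the two headings apart.

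**3. Compare the outcome lists.** The Abstract names complications and adverse events as separate secondary outcomes. The outcome section names complications only. Whether a between-arm adverse-event comparison is planned depends on which list is followed.

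**4. Direction and size.** Let p be the true risk, equal in both arms, and let c_E and c_C be the probabilities that an event is captured in the experimental and control arms. Then

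apparent risk ratio = (p × c_E) / (p × c_C) = 1/s, where s = c_C / c_E.

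Prompting in the experimental arm only implies s < 1, so the ratio exceeds 1 and the error runs against the syringe. The article gives neither p nor s. The values below are assumptions:

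- s = 0.75: 1/0.75 = 1.33
- s = 0.50: 1/0.50 = 2.0
- s = 0.25: 1/0.25 = 4.0

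The apparent risk difference is p × c_E × (1 − s). With c_E = 1 and s = 0.50, an assumed p of 10%, 20% or 30% gives a spurious difference of 5, 10 or 15 percentage points. These figures show how the bias works. They do not estimate it.

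**The case against.** The strongest reply is that the harms one would expect from nipple suction are already recorded in both arms. Complications are in both diaries and are a between-group outcome at 1 week and at 1, 3 and 6 months, and day 1 records sore nipple and pain without restriction by arm. The Ethics approval section frames its safety expectation in terms of pain and sore or bleeding nipples. This stands, and it limits the point. A reader might infer that the safety claim has no control rate at all. The article does not support that for the listed complications.

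A reader might also infer that no control event could be recorded in the first month. That goes too far. The Ethics approval section promises collection of any adverse events without restriction by arm, and the later calls may recover earlier events by recall. But the promise names no instrument or time, and recall at 3 months is not equivalent to a diary entry. The gap may be smaller; it is not closed.

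It would be tempting to compute a significance level for a false excess. That would need an event rate, complete absence of control capture and full follow-up. The article gives no rate, does not imply zero capture, and plans for 50% attrition.

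Two further limits stand. The schedule figure and the diary forms are not available here and may show an adverse-event item for both arms. That the first month is when the syringe is used most is a reasonable inference from a day-1 start and use before every feed, but the article says only that use lasts as long as the mother needs it.

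**Conclusion.** The point holds in a limited form. Following the article as written, adverse events in the first month are prompted in the experimental arm and not in the control arm, and both arms are first asked the same question at month 3. Any between-arm comparison that includes those events is tilted against the syringe. The affected events are those outside the complications recorded in both arms and those that fit either heading. The Abstract and the outcome section also disagree on whether adverse events are an outcome.

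The size is unknown, because it depends on an event rate and a relative capture that the article does not give. The direction rests on one assumption: that a diary prompt raises reporting. The primary outcome is untouched, and the bias would not falsely favour the technique. This is an inexpensive improvement to a secondary outcome and does not threaten the trial's main conclusion.

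**What to change.** - Put the same adverse-event item, with the same wording, in both diaries. Keep daily syringe compliance as the only arm-specific item.
- Ask one identical adverse-event question of both arms at the day-7 call and at the 1-month visit, in addition to the month 3 and 6 calls.
- Add adverse events, compared by randomised arm, to the Secondary outcome measures section so that it agrees with the Abstract. State how an event that is also a breastfeeding-associated complication is to be classified.
- If the schedule figure or the diary forms already provide for this in both arms, correct the Control group text to say so.

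The cost is one diary page and one question at contacts already planned. For women whose first month has already passed, report first-month adverse events descriptively, and note that the prompt differed by arm.
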